### Data analysis

#### Study 1

The research team will conduct statistical analyses using R. The cross-sectional study will characterize the study population through descriptive and multivariate analyses (e.g., Chi-square/Fisher’s exact tests, correlation tests, ANOVA, etc.). We will adhere to the STROBE guidelines for epidemiological studies [58]. A significance level of 0.05 will be applied for statistical analysis.

#### Study 2

A thematic analysis of the data from the semi-structured interviews will be conducted using NVivo 15 software. Moreover, the findings from the Rorschach test will be analyzed using a methodology for interpreting projective material [48], with the aim of highlighting underlying psychic processes, particularly those related to attachment dynamics early traumas, the defensive mechanisms of participants. Additionally, the interviews reported from the AAI assessment will be coded by MN and AF under the supervision of a certified reliable coder [name] using the Adult Attachment Scoring and Classification System [49].

#### Study 3

For the group intervention, a Bonferroni correction will be applied to all *p*-values in t-tests. Cronbach’s alpha will be used to assess the reliability of the scales. Various analyses will be conducted to evaluate pre- and post-intervention effects as well as dose-response effects, including Student’s t-tests, repeated-measures ANOVA, and linear regression.

Primary and secondary outcomes will be analyzed using linear mixed models, incorporating a random group effect if estimation permits. The primary outcome measure is the variation in the total score on the ATSPPH-S at 9 months, calculated using dimensional scoring algorithms. Changes in the primary outcome and the relative effectiveness of the four intervention modalities will be assessed using mixed regression models, utilizing all available data while accounting for participant, time, and group levels. The underlying distribution for the mixed regression model will be determined based on residual distribution.

Per-protocol analyses will also be performed to test robustness. ANCOVA analyses may be conducted as needed to control for confounding variables that could influence the results. If data distribution is non-parametric, analyses such as Mann-Whitney, Wilcoxon, and Kruskal-Wallis tests will be employed.

Missing data will be reported and managed using appropriate imputation methods depending on their proportion and classification (MCAR, MAR or MNAR). However, if the proportion of missing data is very large (> 40%), we will present only the results of the complete case analysis [59].

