## Methods/design

This research project is therefore structured around three complementary phases of study (Table 1), each based on a distinct methodological approach:

A **cross-sectional study (study 1)** that relies on a quantitative approach, conducted through the dissemination of online standardized questionnaires and scales (see: Measures) to young adults residing in partner structures at both regional and national levels. Its objective is to identify factors associated with addictive behaviors and to explore the links between trauma, migratory trajectories, food insecurity, psychological distress and perceived representations and barriers to accessing psychological care. These tools enable the rigorous collection of quantitative data and a multidimensional assessment to model the relationships between factors associated with the psychological and social challenges faced by this population. This study provides insights into general statistical trends.A **qualitative study (study 2)** adopting an exploratory perspective and aiming an in-depth understanding of the representations, subjective experiences, and individual and relational dynamics associated with addictive behaviors and trauma. The qualitative study builds upon the findings of Phase 1 by collecting clinical insights that provide a deeper understanding of the subjective dynamics of participants dealing with substance use issues and the obstacles encountered in their life trajectories that shape their relationship with care services.A **longitudinal study (study 3)** structured around a group intervention called the “Well-Being coffee group”, which operates as an open group (8 to 12 participants per session), conducted over six sessions, each lasting 1.5 to 2 h, held in the evening (6–8 PM) once a month for six months. Participation is voluntary for young residents in THP. The study aims to evaluate the impact of this group discussion format on participants’ psychological well-being, their perceptions of mental health, and their access to care.

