Participants are assessed at multiple time points (T0: prior to the program, T1: mid-program, T2: end of the program, T3: post-program follow-up). These longitudinal evaluations, based on standardized tools, will enable a detailed analysis of participants’ well-being progression and the specific effects attributable to the group intervention. This study is part of an action-research framework, integrating clinical intervention with the production of scientific knowledge while offering transferable recommendations for other support programs aimed at vulnerable young adults.

**Table 1 Tab1:** Summary table of the research methodology

	Study 1	Study 2	Study 3
Type of study	Quantitative	Qualitative	Longitudinale
Method	Cohort study using self-administered questionnaires	Semi-structured interviews Rorschach test Adult Attachment interview (AAI)	Group intervention Self-administrated questionnaires
Eligibility criteria	Participant aged > 18 Resident in a Housing center Fluent in French adult participants who are not under guardianship (tutelle) or curatorship (curatelle).	Participant aged > 18 Fluent in French Any substance user Migratory background	Same as study 1
Exclusion criteria	Minors Do not speak and read French Under Guardianship or Curatorship	Minors Do not speak and read French Under Guardianship or Curatorship	Minors Do not speak and read French Under Guardianship or Curatorship
Main Outcomes	Substance use prevalence Mental health representations Mental health aspects (anxiety, depression) Childhood trauma	Substance use, trauma and migration trajectory (semi-structure interview) Attachment style (AAI tool) Psychological functioning (Rorschach test)	Substance use Perception of mental health care Wellness
Analysis	Quantitative analysis	Thematic analysis	Quantitative and qualitative analysis

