The longitudinal study will follow the same inclusion criteria as the qualitative study (Study 2). However, participation in the group sessions is open to all volunteers for each session, regardless of whether they are substance users. Informed consent will be systematically obtained before each session, ensuring fully informed participation. Promotion of the groups will be conducted through widespread dissemination of informational posters, email communications via the management of the partner structures, and during informational meetings. A follow-up meeting will be organized 15 days later to conduct the initial T0 evaluation with the volunteers.

The “Well-Being coffee group” intervention is implemented in several formats (see Fig. 1). Some groups will take place in person, others via videoconference, all conducted by the same psychologist throughout the sessions. Additionally, a control group will consist of participants who underwent the initial evaluation (T0) but did not attend any sessions. The inclusion of this control group allows for the assessment of changes in psychological and behavioral outcomes over time, comparing those who received the intervention to those who did not. The choice of this comparator was made based on feasibility and ethical considerations, ensuring that participants were not deprived of potential care while maintaining an adequate framework for evaluating the intervention’s effects. Across all formats, participation is voluntary, following a prior information phase and the signing of an informed consent form. Participants will complete standardized evaluation questionnaires at multiple time points (T0, T1, T2, T3).

The discussion groups aim to provide a supportive and open space for free expression. Their objective is to allow participants to articulate their thoughts, emotions, and personal experiences, as well as those evoked by group discussions on various themes, including identity, substance use, migratory experiences, and mental health. The impact of the intervention will be assessed regularly using standardized tools to measure levels of anxiety, depression, and changes in attitudes and willingness to seek help. Finally, a global satisfaction scale will be used at the end of the sessions to collect participants’ subjective feedback on their experiences within the groups (see Fig. 1).

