### Safety considerations

No adverse effects are expected. The questionnaires selected for this study have widely been used in previous research with self-administrated protocols. Meanwhile, the semi-structures interviews from study 2 and focus groups from study 3 may bring up difficult life events. In cases where participation leads to distress or emotional discomfort, participants will receive support and compassionate guidance from the investigator/psychologist conducting the interview, as well as during an individual debriefing following the group sessions. If an urgent need for care is identified, participants will be referred to appropriate socio-medical services for further support.

The findings of the study will be published and shared with the scientific community including scientific publications, conference posters and oral presentations in national and international conferences.

Withdrawal from any phase of the study will be considered if participants revoke their consent during data collection, if they discontinue attendance at research interviews, or if they cease participation in group sessions. Withdrawal is entirely voluntary and will not result in any consequences, ensuring adherence to ethical research principles.

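### The Study 3 dose-response analysis relates outcome to self-chosen attendance with no fixed adjustment, so its slope can be biased in either direction

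*Protocol article*

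**What the plan says.** The protocol article, Data analysis (Study 3), gives one list of methods for two aims, pre/post effects and "dose-response effects, including Student’s t-tests, repeated-measures ANOVA, and linear regression". Linear mixed models are reserved for the primary and secondary outcomes and for comparing the modalities. They account for participant, time and group. The section also allows ANCOVA for confounding if it is thought necessary, without naming covariates or linking it to dose.

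The amount of exposure is left to the participant. Methods/design describes an open group, "conducted over six sessions, each lasting 1.5 to 2 h, held in the evening (6–8 PM) once a month for six months", and adds: "Participation is voluntary for young residents in THP". Procedures says that "participation in the group sessions is open to all volunteers for each session, regardless of whether they are substance users". The zero end of the scale is also a choice: "a control group will consist of participants who underwent the initial evaluation (T0) but did not attend any sessions".

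The outcome is stated in Data analysis: "The primary outcome measure is the variation in the total score on the ATSPPH-S at 9 months". Safety considerations lists, among the grounds on which withdrawal will be considered, "if they cease participation in group sessions".

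**The concern.** A dose-response slope describes the effect of sessions only if people with different attendance would otherwise have changed alike. Here every level of attendance, from none to six, is chosen by the person whose attitude is being measured. Someone well disposed to psychological help at T0 is plausibly more likely to come to a group led by a psychologist. Someone already becoming more open to help may also come more often.

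These two routes bias the slope in opposite directions. Under the first, keen starters have less room to rise and drift back towards the mean, so more sessions go with less improvement. Under the second, more sessions go with more improvement although the sessions did nothing. None of the three named methods, applied to attendance as it stands, separates either pattern from a real effect. A true benefit could be hidden or look like harm, or a gradient could appear where there is none.

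**Working it through.** **The plan's own figures.** The article gives no figure for the dose-response analysis. Its 55 per modality (Participants, Study 3) is reproduced by an exact two-sided t-test with d = 0.7, alpha 0.05 and 95% power, a power the article does not state. That calculation concerns a comparison of groups, not a slope on attendance.

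**Inputs from the article.** Sessions run from 0 to 6. The outcome is change in ATSPPH-S. The significance level is 0.05. The sample is 55 per modality.

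**Assumptions, not in the article.**
- Dose means sessions attended.
- T3 is the 9-month assessment.
- There are 110 attenders (2 × 55, two attending modalities).
- The T0-T3 correlation is 0.5.
- The log-odds of attending each session rise by 0.25, 0.5 or 1.0 per SD of whatever drives attendance.
- The true session effect is zero.

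**Case A: T0 attitude drives attendance.** With standardised scores, T3 = 0.5 × T0 + error, so change = T3 − T0 = −0.5 × T0 + error. The SD of change is √(2 × (1 − 0.5)) = 1, so change correlates −0.5 with T0. Sessions correlate positively with T0, so the slope of change on sessions is negative with no effect at all.

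| Analysis (true effect zero) | 0.25 | 0.5 | 1.0 |
|---|---|---|---|
| Change regressed on sessions | 34% | 78% | 98% |
| t-test of change, 4 or more sessions versus fewer | 24% | 60% | 92% |
| T3 on sessions with T0 in the model | about 5% | about 5% | about 5% |

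In the regression on change, at least 99.9% of the false positives are negative. With a T0-T3 correlation of 0.7 the first row becomes 23%, 56% and 86%. With two time points, the group-by-time test of a repeated-measures ANOVA is the t-test on change, so using T0 as a time point does not remove the problem.

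**Case B: an unmeasured trait, correlated 0.3 with change, drives attendance.** Change regressed on sessions is falsely significant in about 15% to 66% of trials over the same range of attendance slopes, now with a positive slope. With T0 in the model the rate is still about 13% to 52%. If the trait is constructed to be independent of T0, adjustment leaves about 17% to 78%.

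**Second check, other assumptions.** Here n = 165, the test-retest correlation is 0.7 and the log-odds slope is 0.5 to 1.0. The columns give the correlation of the attendance trait with spontaneous change.

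| | 0 | 0.1 | 0.2 | 0.3 |
|---|---|---|---|---|
| Change on sessions | 5-6% | 10-15% | 25-49% | 50-84% |
| Adjusted for T0 score only | 5-6% | 10-15% | 25-47% | 44-83% |
| Spurious difference, 0 to 6 sessions | about 0 | about 0.2 SD | 0.35-0.4 SD | 0.5-0.6 SD |

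Adjusting for the trait itself returns 4% to 6%. If attendance is unrelated to the trait, every method stays near 5%.

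**The case against.** The strongest reply is that the article does not say what a critical reader may infer from it.

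- **Unadjusted analysis.** A reader might infer that the regression omits T0. The text says only linear regression, and ANCOVA is permitted in the same section. A covariate list and a definition of dose could sit in an analysis plan that is not shown. This stands: omission of T0 is an inference. But the article itself names the methods and makes confounder control optional and unconnected to dose, so the plan as written permits the biased analysis.
- **t-tests and ANOVA for dose.** The single list also covers pre/post effects, and regression may be the only method meant for dose. This stands, so the other two are only possible dose analyses.
- **Efficacy claim.** A reader might infer that the slope will be presented as proof of benefit. Methods/design does speak of "the specific effects attributable to the group intervention", but that concerns the longitudinal evaluations in general. No section gives dose-response such a role.
- **Low attenders removed.** A reader might infer that those who stop coming leave the data. Safety considerations says only that withdrawal will be considered, sessions are open one by one, zero-session participants are retained as controls, and the mixed models use all available data. The text leaves room for such losses but does not prescribe them.
- **Direction.** Case A makes sessions look harmful, so its 34% to 98% cannot illustrate false support for efficacy. That is correct. Only Case B points that way.

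**Conclusion.** The concern holds in a limited form. The article commits to a dose-response analysis of self-selected attendance and fixes no adjustment for it. The outcome is a plausible cause of attendance, so the slope can be wrong in either direction: mostly negative if T0 attitude drives attendance (about 34% to 98% false findings), positive if an unmeasured readiness to change does (about 15% to 66%). T0 adjustment cures the first case and not the second. All these rates depend on assumed attendance slopes and correlations, and they fall to about 5% if attendance is unrelated to readiness.

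Dose-response is a supporting analysis, and this point does not concern the mixed-model specification for the primary outcome. The documents do not support the stronger statements that the regression is certainly unadjusted, that a gradient will be reported as efficacy, or that low attenders will be dropped. The change is still worth making because the better analysis uses scores already planned at T0.

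**What to change.** 1. Define dose as the number of sessions attended before each assessment and analyse it in the mixed model, with T0 ATSPPH-S, PHQ-9, GAD-7 and residence/group as fixed covariates.
2. Use this in place of any unadjusted t-test, ANOVA or regression on attendance. The pre/post use of those methods is a separate matter.
3. Keep the questionnaire data of participants who stop attending but still consent to assessment, at their actual dose, and align the withdrawal wording in Safety considerations with this.
4. State in advance that the slope is an association and does not count as evidence of efficacy. This is essential, because T0 adjustment removes only selection on measured baseline variables. It does not deal with unmeasured readiness or with attendance that responds to how a person is progressing.

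The cost is mainly wording. The T0 scales are already planned. An attendance record is needed for any dose analysis, and some effort goes into following people who stop coming. The downside is a weaker claim from the dose-response analysis.

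### Study 3 groups are formed by attendance, so a per-protocol set based on attendance repeats or deepens the self-selection and cannot test the robustness of the control comparison

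*Protocol article*

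**What the plan says.** All references are to the protocol article. The Data analysis section, Study 3, names the analysis and its purpose in one sentence: "Per-protocol analyses will also be performed to test robustness". The same section defines the outcome, "The primary outcome measure is the variation in the total score on the ATSPPH-S at 9 months", and says that the main mixed regression models will be fitted "utilizing all available data while accounting for participant, time, and group levels". Adjustment for confounders by ANCOVA is optional there, and no covariates are named.

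The exposure is described in two other sections. Under Methods/design, the intervention "operates as an open group (8 to 12 participants per session), conducted over six sessions", and "Participation is voluntary for young residents in THP". Under Procedures, Study 3, "participation in the group sessions is open to all volunteers for each session, regardless of whether they are substance users", and "a control group will consist of participants who underwent the initial evaluation (T0) but did not attend any sessions". No minimum number of sessions is stated and no random allocation is described. Under Safety considerations, withdrawal is considered in several situations, one of which is "or if they cease participation in group sessions".

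**The concern.** A per-protocol analysis can support a main result when the groups were fixed independently of adherence. The main analysis then keeps the groups comparable, the per-protocol analysis relaxes that, and the reader learns whether the conclusion depends on the choice. Here adherence is what forms the groups. A person becomes a control by not attending, and sessions are joined one at a time by choice. The main contrast is already attenders against non-attenders, so an adherence-based subset has no separate, protected comparison to be checked against.

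The outcome makes this more than a formality. ATSPPH-S measures attitude to seeking professional psychological help, and willingness to come to a psychologist-led group is plausibly related to it. Readers commonly take agreement between main and per-protocol results as reassurance. In this design such agreement would be expected from self-selection alone.

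**Working it through.** **Step 1. The possible attendance definitions.** The article defines controls by zero sessions. I take the intervention side of the main contrast to be everyone who attended at least one session; this is an assumption.

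- Any attendance counts as compliance: the per-protocol set is the same attenders against the same controls, and the estimate is identical.
- A session threshold applies, or those who stop are removed: only attenders can be removed, because a control attends nothing by definition. The intervention side is thinned and the control side is untouched. The withdrawal ground under Safety considerations makes this a natural reading, since only an attender can cease attending.

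A set that excludes only other deviations, such as ineligibility, leaves the attendance selection as it was and so does not test it.

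**Step 2. Illustration with no true effect.** The plan gives no figure for this analysis. The nearest is the planning effect of d = 0.7 with 55 per modality. That reproduces for a two-sided t-test at alpha 0.05 with an implied power of 95% (54.02, rounded up; power 95.3% at 55), but nothing below depends on it. Let r be the correlation between willingness to attend (z) and change in ATSPPH-S. The documents do not give r, so every value is assumed.

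*Attendance model A: thirds, closed form.* Lowest third of z = controls, upper two thirds = attenders, top third = high-attendance subset. The cut-points are ±0.4307, where the normal density is 0.3636.

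- Mean z: controls −0.3636/(1/3) = −1.091; attenders 0.3636/(2/3) = 0.545; top third 1.091.
- Gaps from controls: 1.091 + 0.545 = 1.636, and 1.091 + 1.091 = 2.182.
- Variance of z within an outer third: 1 + 0.4307 × 1.091 − 1.091² = 0.280. Within the upper two thirds: 1 − 0.4307 × 0.545 − 0.545² = 0.468. Pooled 1:2 for the main contrast: (0.280 + 2 × 0.468)/3 = 0.405.
- d = r × gap / √(1 − r²(1 − within-group variance of z)).
- r = 0.3, main: 0.3 × 1.636 / √(1 − 0.09 × 0.595) = 0.491/0.973 = 0.50.
- r = 0.3, subset: 0.3 × 2.182 / √(1 − 0.09 × 0.720) = 0.655/0.967 = 0.68.
- r = 0.2, same formula: 0.33 and 0.44.

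A simulation of 2,000,000 draws gives the same four values.

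*Attendance model B: session counts, simulation.* 165 people (3 × 55). One third never attend, chosen on motivation plus noise. The others attend 1 to 6 sessions with a probability that rises with motivation. There were 2,000 replicates, each analysed by a t-test rather than the planned mixed model. Differences are in units of the SD of change; false-positive rates are in brackets.

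| r | Main, and any-attendance set | At least 4 of 6 sessions | 6 of 6 sessions |
|---|---|---|---|
| −0.2 | −0.23 (29%) | −0.32 (41%) | −0.44 (25%) |
| 0 | 0.00 (5%) | 0.00 (5%) | 0.01 (5%) |
| 0.1 | 0.12 (12%) | 0.16 (15%) | 0.23 (10%) |
| 0.2 | 0.23 (29%) | 0.33 (41%) | 0.43 (25%) |
| 0.3 | 0.34 (55%) | 0.49 (75%) | 0.64 (49%) |

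About 57 people remain at four or more sessions and about 11 at six of six, which is why the last column has lower rejection rates despite larger differences.

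**Step 3. Reading across.** The any-attendance set reproduces the main estimate exactly. Whenever r is not zero, the threshold sets move further from zero in the same direction as the main estimate. Models A and B differ in size but agree on this ordering. For r = 0.2 to 0.3 they span 0.23 to 0.50 for the main contrast and 0.33 to 0.68 for a high-attendance subset (the top third in A, four or more sessions in B).

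**The case against.** The strongest reply is that the article does not define the per-protocol set, and that a condensed article may leave this to the full protocol or analysis plan. That is right, and the absent definition is not the point made here. A reader might infer that the analysis keeps only the keenest attenders. The documents do not say so: that is one reading, and a set with no threshold would select no one. Nor do they say how the per-protocol result will be interpreted.

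A reader might also infer that the check will tend to confirm a false benefit. That needs a positive r, which the documents do not supply. The outcome is a change score, so keen attenders could start higher and gain less, and the bias would then run the other way.

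Three further objections stand. Between active formats, an attendance threshold would apply to both sides, so the point is limited to the comparison with controls. A per-protocol set may also serve legitimate purposes unrelated to dose. And the root of the problem is the attendance-defined control group, which affects the primary contrast whether or not this analysis is run.

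What the objections do not rescue is the stated purpose. No attendance-based definition supplied elsewhere would make the analysis a test of robustness for the control comparison.

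**Conclusion.** The point holds in limited form. For the intervention-versus-control comparison, a per-protocol analysis based on attendance either duplicates the main contrast or applies further self-selection to one side, so its agreement with the main result carries no evidence of robustness. This follows from the article's own definition of the control group and needs no numerical assumption.

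The size does need assumptions. With r of 0.2 to 0.3 and no true effect, a spurious d of about 0.23 to 0.50 in the main contrast becomes about 0.33 to 0.68 in a high-attendance subset. At r = 0 there is no bias, and at r = −0.2 it is −0.23 and −0.32 (model B). The top of the range lies close to the planning effect of 0.7, but only under model A, where willingness alone decides attendance. It should not be read as a forecast. The conclusion that survives any sign of r is that the check cannot expose the bias that most threatens the result.

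**What to change.** In Data analysis, Study 3:

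- Stop describing the per-protocol analysis as a robustness test for the intervention-versus-control comparison.
- If an attendance-based subset is kept, fix its session threshold before outcome data are seen, label it descriptive, and state that it shares or amplifies the self-selection of the main contrast.
- As the robustness check, keep the non-attending controls as comparator and repeat the primary mixed model adjusted for a covariate set named in advance from the T0 measures: ATSPPH-S, PHQ-9, GAD-7, AUDIT, Fagerström and CAST. State that this removes selection only as far as these measures capture it, and that unmeasured motivation remains.

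Regrouping everyone with a T0 by the format offered or chosen should not be used as the check on the control contrast. It would move the non-attenders into the format groups and remove the untreated comparator.

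The cost is a change of wording and one additional model on data the study already plans to collect. The sponsor also gives up a supporting result that would probably look favourable if willingness to attend and score change are positively related. The change does not cure the confounding in the primary contrast, but it stops the plan from presenting a second view of it as reassurance.

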### Participants

#### Study 1

We based our calculations on an approximate population size of 60,000 young individuals supported throughout the previous year (Year N-1) across the entire territory. The margin of error was set at 5%, with a confidence level of 95%. We applied Cochran’s formula (Z² × p × (1-p) / E²) to determine the required sample size. Accordingly, the sample size necessary for this cross-sectional study is 382 respondents.

#### Study 2

We will base our qualitative study on a sample of 30 young volunteers recruited independently of the cross-sectional study, following the procedures outlined below. However, participant inclusion will continue until data saturation is reached. Data saturation will be considered achieved when the main themes emerge, meaning that all relevant themes necessary to address the research questions have been identified in the collected data.

#### Study 3

For this study, we estimate a strong effect size of 0.7 (Cohen’s d) with a significance level of 0.05. Based on these parameters, and using the software G*Power 3.1, we determined that 55 participants would be required for each group modality, resulting in a total of 165 participants. To account for an estimated 10% dropout rate, we will include 182 young individuals in the study.

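### The missing-data rule turns on an MCAR/MAR/MNAR label that the data cannot settle, so no test of the 9-month result against informative loss is guaranteed

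*Protocol article*

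**What the plan says.** All of this is in the protocol article; no separate SAP is shown.

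- **Missing-data rule** (closing paragraph of Data analysis): missing data are to be "managed using appropriate imputation methods depending on their proportion and classification (MCAR, MAR or MNAR"). The text does not say how the class is decided or which method belongs to which class.
- **Heavy missingness** (same paragraph): "if the proportion of missing data is very large (> 40%), we will present only the results of the complete case analysis".
- **Primary outcome** (Data analysis, Study 3): "The primary outcome measure is the variation in the total score on the ATSPPH-S at 9 months".
- **Primary model** (same place): mixed regression, "utilizing all available data while accounting for participant, time, and group levels".
- **Robustness** (same place): "Per-protocol analyses will also be performed to test robustness". No other robustness analysis is named for Study 3.
- **Withdrawal** (Safety considerations): a participant may be counted as withdrawn "if they discontinue attendance at research interviews, or if they cease participation in group sessions".
- **Planning values** (Participants, Study 3): "we estimate a strong effect size of 0.7 (Cohen’s d) with a significance level of 0.05", 55 per modality, 165 in total, and 182 after allowing for 10% dropout.

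**The concern.** The rule chooses the imputation method from the class of the missingness mechanism. MCAR can be contradicted by observed data, for instance if loss is related to T0 scores. MAR and MNAR cannot be told apart in this way, because they differ only in how missingness depends on values that were not recorded. An SAP could attach a method to each class, but it could not make the MAR/MNAR branch decidable from the data. The branch is therefore taken by judgement once the pattern of loss is known, and that judgement decides whether informative loss is examined at all.

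This matters here because the primary outcome is an attitude to seeking psychological help, and the intervention is a psychologist-led discussion group. Leaving the group, or no longer answering the questionnaire, may well be related to that attitude. Ceasing to attend sessions can count as withdrawal, a route that does not exist for controls, who by definition never came to a session. Loss may therefore differ between arms. The named per-protocol analysis does not address this, since it tends to remove the people who stopped attending.

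Two further points in the same paragraph add to the uncertainty. It does not say whether imputation precedes, supplements or replaces the mixed model. And above 40% missing it withdraws everything except the complete-case result.

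**Working it through.** **1. The plan's own figures.** A two-sample t-test with d = 0.7 and two-sided alpha 0.05 needs 55 per group for 95% power (power at 55 is 0.953). The article states neither power nor sidedness, so both are inferred. Then 3 × 55 = 165, and 165 × 1.10 = 181.5, which rounds to 182. The planning values reproduce. The two that matter below are the effect of 0.7 and the planned loss of 10%.

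**2. Can the rule be followed from data?**

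| Distinction needed | Can observed data inform it? |
|---|---|
| MCAR versus not MCAR | Partly: data can speak against MCAR |
| MAR versus MNAR | No: it depends on the unseen values |

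The second distinction can rest only on assumption, for example from recorded reasons for loss.

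**3. What could be at stake.** Let m be the share missing at 9 months, and δ the amount (in SD) by which unseen participants score below their MAR prediction. A MAR analysis overstates an arm mean by m × δ. The bias in the contrast is

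bias = m(attenders) × δ(attenders) − m(controls) × δ(controls).

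The article gives no δ. Assume 0.3 to 0.5 for attenders and 0 for controls:

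| Missing among attenders | Bias at δ = 0.3 | Bias at δ = 0.5 | Share of 0.7 |
|---|---|---|---|
| 10% (planned) | 0.10 × 0.3 = 0.03 | 0.10 × 0.5 = 0.05 | 4% to 7% |
| 25% (assumed) | 0.25 × 0.3 = 0.075 | 0.25 × 0.5 = 0.125 | 11% to 18% |
| 40% (the plan's cut-off) | 0.40 × 0.3 = 0.12 | 0.40 × 0.5 = 0.20 | 17% to 29% |

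With equal m and equal δ in both arms the two terms cancel and the bias is 0. If m × δ is larger among controls, the sign reverses and the benefit is understated.

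**4. Effect on the test.** A simulation used no true effect, 55 per arm, a baseline-outcome correlation of 0.5, loss in one arm depending on the outcome (log-odds 1 per SD, low scorers lost more often), and the same share lost at random in the other arm. The comparison was adjusted for baseline.

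| Missing | Bias (SD) | Two-sided type I error (nominal 5%) |
|---|---|---|
| 10% | 0.07 | 6.9% |
| 20% | 0.13 | 11.0% |
| 40% | 0.26 | 23.9% |

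Dividing bias by share missing gives a shift of roughly 0.65 to 0.7 SD. This is a harsher, one-sided case than step 3 and should be read as such.

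**5. The 40% rule beside the primary model.** The mixed model keeps every participant with any usable measurement. The complete-case rule discards the partial records and is generally valid only under MCAR or covariate-dependent missingness. It takes over in the range where m, and so the possible bias, is largest, and it rules out presenting any sensitivity analysis there.

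**The case against.** Several stronger readings are tempting, and the article does not support them.

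- **That the rule cannot be carried out.** The article does not say the class will be derived by a test. A class can be assumed from reasons for loss and subject knowledge. The rule is discretionary, not impossible.
- **That the 9-month result gets no test against informative loss.** Up to 40% missing, MNAR is listed as a case to be handled, so such an analysis is not excluded. Naming the technique is commonly left to a full protocol or SAP, and its absence from an article is no fault. What stands is that the test is conditional on an unverifiable label and is therefore not guaranteed.
- **That imputation contradicts the mixed model.** The two can coexist, for example through imputation of unanswered questionnaire items or missing covariates, or for the t-tests and ANCOVA also listed. The relation is unstated, which is an ambiguity. The actual conflict is between the all-available-data model and the complete-case-only rule above 40%.
- **That a MAR result overstates the benefit.** Controls are volunteers who completed T0 and then attended nothing. Loss of interest in psychological help is at least as plausible among them, so the sign of the bias is open.
- **That the effect is large.** At the planned 10% dropout it is small, at most 0.05 SD under the assumptions used.

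These objections narrow the point but do not remove it. The article states a decision rule, and no further document can make its MAR/MNAR branch decidable from the data.

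**Conclusion.** The point holds as a weakness in a stated rule and should be corrected. A judgement that the data cannot check, made after the losses are seen, decides how missing 9-month ATSPPH-S scores are treated and whether informative loss is examined. Above 40% missing, the plan itself excludes that examination.

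On size, the possible bias runs from minor at the planned dropout to more than a quarter of the planned effect at the plan's own cut-off. These figures rest on an assumed shift among attenders and none among controls. They illustrate what is at stake and do not predict a bias in favour of the intervention. Confidence is medium, because the actual loss and any SAP are unknown.

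**What to change.** Change the closing paragraph of Data analysis as follows.

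1. Delete the dependence of the method on MCAR, MAR or MNAR.
2. State that the primary analysis is the Study 3 mixed model on all available data, under MAR, with T0 scores in the model.
3. Always report one prespecified MNAR sensitivity analysis: arm-specific delta-adjusted multiple imputation of the 9-month ATSPPH-S. Vary the shift in both arms (for example 0 to −0.5 SD), since the direction is not known, and report the tipping point.
4. Remove the rule that only complete-case results are presented above 40% missing. A complete-case result may still be shown beside the others.

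The cost is a few sentences and one extra analysis in R, with no new data. The change should be made before outcomes are examined. The Trial status section requires prior ethics committee approval for substantial modifications, so the sponsor would need to decide whether this is one.
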